### Sample size

Sample size calculation is based on the rate of patients experiencing the primary endpoint objective best overall response (CR or PR). It is the aim of this phase II study to come to a decision whether the experimental treatments VPA and ATRA are promising treatment options being worthy of further investigation in phase III. Therefore, it is not necessary and desired to come to a definitive and rigorous statistical proof of the efficacy of VPA and ATRA in this study. Nevertheless, statistical tests on the effects of VPA, i.e., (DAC + VPA) and (DAC + VPA + ATRA) vs. (DAC) and (DAC + ATRA), and ATRA, i.e., (DAC + ATRA) and (DAC + VPA + ATRA) vs. (DAC) and (DAC + VPA), will be conducted. Both tests will be performed at a one-sided significance level of 10 %. Based on the results of our single-arm Phase II study of DAC in AML (Study 00331, NCT00866073) [22], which has recruited 235 patients in Germany, an objective best overall response rate (ORR) of about 25 % in treatment arm (DAC) is assumed. The study should have a power of 80 % to detect an increase in the ORR, when the ORR after application of VPA or ATRA is about 40 %. This corresponds to an odds ratio of 2 between the treatment arms no VPA vs. VPA and no ATRA vs. ATRA, respectively. It is further assumed that VPA and ATRA do not show an antagonistic effect. With these assumptions, 176 patients have to be included in this study. This was calculated with formula (3) in Campbell et al., 1995 [23] for the Chi square-test of the hypothesis that the difference between the rates is equal to zero, and is adequate also for analysis with logistic regression [24]. To account for the possibility of some protocol violations, 200 patients will be randomized in total (ratio of 1:1:1:1 to the four treatment arms).

### Randomization

Center-stratified block randomization with randomly varying block size is performed based on computer-generated lists. Block sizes are documented separately from the study protocol in a document not accessible to investigators. Randomization is performed centrally in order to guarantee concealment of treatment allocation. Blinding of the VPA and ATRA intake is impossible since serum levels of VPA will be measured, and therefore placebo control will not be feasible. However, concealment of randomization will be guaranteed to minimize selection bias, and reviewers of response will be blinded with regard to the patient’s treatment arm to minimize assessment bias.

### Statistical analysis

The primary efficacy analysis of this clinical trial will be conducted according to the intention-to-treat principle. This means that the patients will be analyzed in the treatment arms to which they were randomized, irrespective of whether they refused or discontinued the treatment or whether other protocol violations are revealed. The analysis of the effects of the different treatment schedules (VPA vs. no VPA and ATRA vs. no ATRA) with respect to the primary endpoint objective best overall response will be performed with a logistic regression model. The treatment effects will be tested using the Wald test at a one-sided significance level of 10 %, and as estimates of the effect sizes the odds ratios will be given with 95 %-confidence intervals. A multiplicative interaction effect between VPA and ATRA will be included in the logistic regression model and its size will be estimated with 95 %-confidence interval. The analysis of the treatment effects with respect to the secondary endpoints PFS and OS will be performed with the Cox model. The analysis of the treatment effects with respect to the secondary endpoint overall best response (CR, PR and ALE) will be performed with a logistic regression model. The PFS rates and the OS rates of the different treatment arms will be estimated by the Kaplan-Meier method, and the ORR of the different treatment arms will be estimated as relative frequencies. For evaluating QOL, scores will be calculated according to Fayers et al., 2001 [25]. At the different time points during follow-up changes in relation to baseline will be calculated. With respect to the secondary endpoints QOL and number of nights in hospital, the treatment groups will be compared descriptively.

Safety is analyzed in the safety population including all randomized patients who received at least one dose of study medication, and patients are analyzed according to the received treatment. AEs are coded using Medical Dictionary for Regulatory Activities (MedDRA). The incidence of AEs is calculated as the number of patients who experienced at least one AE of a certain category as a percentage of the total number of patients in the safety population.

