### Serial assessment of patient fitness and psychological state

As in the predecessor phase II trial in elderly, non-fit AML patients receiving DAC (study 00331, NCT00866073), systematic functional assessment of the patients is being conducted prior to randomization and at several defined time points during and after the study treatment [27]. It is an additional aim of the study to investigate the prognostic value of geriatric assessments for elderly AML patients treated non-intensively. This includes determination of the activities of daily living (ADL) by application of the Barthel index, assessment of quality of life by the EORTC-C30 questionnaire, application of the Hospital and Anxiety Depression Scale (HADS), and determination of psychological resilience by application of the RS-11 questionnaire. In addition, the performance status (Eastern cooperative oncology group performance status, ECOG) of the patient is captured before and at defined time points during the treatment. Comorbidities are scored prior to treatment using the Hematopoietic Cell Transplantation-Comorbidity Index (HCT-CI). The compliance with this functional assessment is >90 %.

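### The primary response model, as described, names no baseline covariate and no centre term; adjusting for data already collected could add 0 to about 8 points of power

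*Protocol article*

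**What the plan says.** The Statistical analysis section introduces the primary model with "The analysis of the effects of the different treatment schedules (VPA vs. no VPA and ATRA vs. no ATRA" as its target. It then states logistic regression, a Wald test at one-sided 10 %, odds ratios with 95 % confidence intervals, and a multiplicative VPA-by-ATRA interaction. No other term is named. For PFS and OS, both secondary, it says only that a Cox model is used; no terms are listed and no interaction is mentioned.

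The Randomization section gives the allocation method: "Center-stratified block randomization with randomly varying block size is performed based on computer-generated lists". Centre is the only stratification factor named. The Study design and setting section lists 28 sites.

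Baseline data are plentiful. Age and primary versus secondary AML appear in the eligibility criteria. Central karyotyping is informative in more than 90 % of patients. ECOG is captured before treatment, and "Comorbidities are scored prior to treatment using the Hematopoietic Cell Transplantation-Comorbidity Index (HCT-CI".

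The Sample size section plans a Chi-square comparison of two rates, described as also adequate for logistic regression: "Both tests will be performed at a one-sided significance level of 10" %, "The study should have a power of 80 % to detect an increase in the ORR", "an objective best overall response rate (ORR) of about 25 % in treatment arm (DAC) is assumed", "when the ORR after application of VPA or ATRA is about 40" %. It requires 176 patients and randomizes 200.

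**The concern.** Response to low-intensity AML treatment plausibly depends on patient and disease characteristics. None of them is balanced by design here, and there are about 50 patients per arm. In a logistic model, adjusting for covariates that truly predict response raises the power of the treatment test. Leaving them out forgoes that gain, although the data cost nothing extra. Stratifying by centre and then leaving centre out of the model is also a mismatch between design and analysis, and it can make the test slightly conservative when centres differ.

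Timing adds to this. Treatment is open-label. According to the Quality assurance system and Study status sections, the interim report showed baseline characteristics by arm and went to the coordinating investigator and medical coordinator as well as the DMC. A covariate list chosen late could therefore be chosen with knowledge of the imbalances. A list fixed in writing beforehand avoids that.

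**Working it through.** **1. The plan's own figure.** Inputs from the Sample size section: rates 0.25 and 0.40, one-sided alpha 0.10 (z = 1.2816), power 0.80 (z = 0.8416). The mean rate is 0.325. With pooled variance and no continuity correction, patients per factor level are

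n = [1.2816·√(2·0.325·0.675) + 0.8416·√(0.25·0.75 + 0.40·0.60)]² / 0.15² = [0.8489 + 0.5503]² / 0.0225 = 87.01, rounded up to 88.

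The total is 2 × 88 = 176, as stated. The odds ratio is (0.40/0.60)/(0.25/0.75) = 2, also as stated ("This corresponds to an odds ratio of 2 between the treatment arms no VPA vs. VPA").

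Power at n per level is Φ[(0.15·√n − 0.8489)/0.6538]:
- n = 88: Φ(0.854) = 80.3 %
- n = 100 (all 200 randomized): Φ(0.996) = 84.0 %

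The unadjusted comparison therefore has its planned power.

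**2. Gain from baseline covariates.** The article gives no prognostic effect, so the strength is an assumed range. In simulation the marginal rates were held at 25 % and 40 %, there was no ATRA effect, the test was a one-sided 10 % Wald test, and one standardised baseline score acted on the log-odds scale. The Monte Carlo error of each power is about 0.7-0.9 points.

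| Score SD (assumed) | N = 176: unadjusted / adjusted, % | N = 200: unadjusted / adjusted, % |
|---|---|---|
| 0 | 81.2 / 81.2 | 84.7 / 84.6 |
| 0.5 | 80.1 / 82.2 | 84.9 / 85.8 |
| 1.0 | 81.5 / 85.1 | 84.5 / 88.6 |
| 1.5 | 80.8 / 88.6 | 84.5 / 91.7 |

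The gains at 176 are 0, 2.1, 3.6 and 7.8 points; at 200 they are about 0, 0.9, 4.1 and 7.2. A single correctly specified score is favourable to adjustment. A simulation with seven covariate terms at N = 200 gave about -1, 0, +3 and +3 points for SD 0, 0.5, 0.8 and 1.0.

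**3. Centre.** There are 28 sites, so 200/28 = 7.1 patients each. Simulation at N = 176 used blocks of 4 within centres and unequal centre sizes (both assumed):

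| Centre SD (assumed) | Unadjusted power, % | Centre-stratified CMH power, % | Unadjusted type I error, % | Fixed centre terms, type I error, % |
|---|---|---|---|---|
| 0 | 80.9 | 79.8 | 9.8 | 11.4 |
| 0.3 | 81.6 | 79.9 | 8.6 | 10.7 |
| 0.6 | 81.5 | 81.2 | 9.3 | 11.4 |
| 1.0 | 82.6 | 84.4 | 9.2 | 12.8 |

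Stratified analysis changes power by -1.7 to +1.8 points. Ignoring centre does not inflate the type I error. Fixed centre terms do, and they also bias the log odds ratio upward (median 0.82 against a true 0.69 when centres do not differ).

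**4. Interaction coding.** The article does not state it. With the interaction in the model and 0/1 coding, the VPA term tests VPA in patients without ATRA, and power at 176 is about 59-61 %. With ±1/2 coding it tests the factor margin, and power is about 80-82 %. Any rewritten model has to keep the second property.

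**5. Room for covariates.** With an effect of one drug only, expected responders are 88 × 0.25 + 88 × 0.40 = 57.2 among 176.

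**The case against.** The strongest objection is that the point rests on silence. A journal article condenses the protocol, the SAP is not shown, and covariate lists are commonly left to it. A reader might infer that the models contain only the treatment terms. The article does not say so; it names those terms and no others. Still, the description of the primary model is detailed and the sample size is that of an unadjusted comparison, so an unadjusted analysis is the natural reading. The request must nevertheless be conditional on the SAP. For the Cox models not even an interaction is stated, so nothing can be said about their content beyond the absence of listed terms.

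Second, the trial loses nothing against its own target. A reader might infer a power shortfall or an invalid test; the reproduced 80.3 % and the type I error near or below 10 % rule out both. This objection stands in full.

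Third, no figure supports calling the covariates strongly prognostic, and the article treats the prognostic value of the geriatric assessments as a study question. This stands too, which is why only a range can be given.

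Fourth, the unadjusted odds ratio lying nearer to 1 than the covariate-adjusted one might be read as bias. It is non-collapsibility. The planned 25 % versus 40 % is a marginal contrast, and the unadjusted model estimates it. The marginal estimate must therefore be kept.

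Finally, this is a phase II screening trial that disclaims definitive proof. That lowers the urgency, but not the value of a nearly free improvement.

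**Conclusion.** The point holds as an advisory on efficiency and prespecification, not as an error. As described, the primary model names VPA, ATRA and their interaction, the Cox models name no terms, and neither uses the collected baseline data or the stratification factor. The possible gain is 0 to about 8 points of power, and about 4 or less unless the covariates are strongly prognostic. It rests on assumed prognostic strength, marginal rates of 25 % and 40 %, and no ATRA effect. The centre component is minor, at about -2 to +2 points. The documents do not support a conclusion that the trial is underpowered, that its test is invalid or that its odds ratio is biased.

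**What to change.** Unless the SAP already does this, fix the following before any unblinded analysis:

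- **Primary logistic model:** VPA, ATRA and their interaction, coded ±1/2 or equivalently so that the VPA and ATRA terms test the factor-margin effects, plus a short covariate list. An example is age, ECOG, HCT-CI, karyotype risk group with a category for missing or non-informative results, and primary versus secondary AML.
- **Cox models for PFS and OS:** the same covariates.
- **Centre:** a random intercept (frailty in the Cox models) or pooled small sites, not 28 fixed effects.
- **Reporting:** the unadjusted odds ratios beside the adjusted ones, because the trial was sized for the marginal contrast.

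The cost is wording; the variables are already part of the study's data collection. The missing category for karyotype is needed because results are informative in more than 90 % of patients rather than all, and the adherence above 95 % in sending samples is quoted only for sites belonging to the AML study group.

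There are two downsides. The adjusted odds ratio is conditional and does not correspond directly to 25 % versus 40 %. And with about 57 responders expected among 176 patients the list must stay short: three treatment terms plus seven covariate terms would leave about 57/10 = 5.7 responders per term.

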## Background

Acute myeloid leukemia (AML) of the older patient constitutes a major unmet clinical need since the large majority will not be found eligible for induction chemotherapy. Reasons for this decision include host factors (comorbidities, reduced performance status, functional limitations due to age), often leading to poor tolerance of repeated chemotherapy courses, as well as the unfavorable biology of this disease in older patients. Among low dose cytarabine, azacitidine or best supportive care, the hypomethylating agent (HMA) decitabine (DAC) represents one of the therapeutic options for these patients providing effectiveness, good tolerability and maintenance of quality of life. In this trial, we ask whether a combination of DAC with the histone deacetylase inhibitor VPA and/or ATRA is able to increase the objective best response rate to DAC alone in AML of the elderly.

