## Methods/Design

### Study design and setting

This is a prospective, randomized, observer blind, active control, parallel group, multicenter, phase II study. The objective of the trial is the investigation of efficacy and safety of the histone deacetylase inhibitor (VPA) and all-*trans* retinoic acid (ATRA) as add-on to the epigenetically active drug decitabine (DAC) in older and unfit acute myeloid leukemia (AML) patients.

The trial has a 2x2 design randomizing the patients to the following four treatment arms: DAC, DAC + VPA, DAC + ATRA, DAC + VPA + ATRA. The effect of VPA will be investigated by comparing the combined treatment arms (DAC + VPA) and (DAC + VPA + ATRA) as experimental group versus the combined treatment arms (DAC) and (DAC + ATRA) as control group, and the effect of ATRA will be investigated by comparing the combined treatment arms (DAC + ATRA) and (DAC + VPA + ATRA) as experimental group versus the combined treatment arms (DAC) and (DAC + VPA) as control group.

Trial sites are located in Aachen, Berlin, Bochum, Braunschweig, Bremen, Düsseldorf (two sites), Esslingen, Frankfurt, Freiburg, Hagen, Halle, Hamm, Hannover, Jena, Koblenz, Lahr, Lebach, Leipzig, Lüdenscheid, Marburg, München, Münster, Offenburg, Ravensburg, Tübingen, Ulm, and Villingen-Schwenningen.

The study and all participating sites were approved by the central ethics committee (University of Freiburg, 76/10) and the respective local ethics committees. Patient’s written consent to participate in this clinical trial and translational research program was obtained prior to any study-specific procedures. The identifying number of the DECIDER trial in ClinicalTrials.gov registry is NCT00867672 and in German clinical trials registry DRKS00000733.

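### The primary logistic model includes the VPA-by-ATRA interaction without saying which contrast the Wald tests address, so the 80% power of the pooled tests depends on an unstated coding

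*Protocol article*

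**What the plan says.** Three sections of the protocol article bear on this point.

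- **Study design and setting** fixes the contrasts as pooled: "The effect of VPA will be investigated by comparing the combined treatment arms" that contain VPA with the two that do not. ATRA is handled in the same way.
- **Sample size** repeats those two pooled comparisons and gives each a one-sided 10% test. It assumes 25% response on DAC and about 40% after VPA or ATRA, and adds: "This corresponds to an odds ratio of 2 between the treatment arms no VPA vs. VPA and no ATRA vs. ATRA, respectively". It also assumes no antagonism and arrives at 176 patients for 80% power. This is a chi-square calculation, of which the article says that it "is adequate also for analysis with logistic regression". In total 200 patients are to be randomized 1:1:1:1.
- **Statistical analysis** names one logistic regression model for the primary endpoint, with VPA and ATRA tested by Wald tests at one-sided 10% and reported as odds ratios with 95% confidence intervals. It then says: "A multiplicative interaction effect between VPA and ATRA will be included in the logistic regression model". The size of the interaction is to be estimated with a 95% confidence interval.

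No separate interaction model, factor coding or averaged contrast is mentioned.

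**The concern.** Once a product term is in a logistic model, the coefficient labelled VPA has no fixed meaning until the coding is given. With 0/1 indicators, the usual default, it is the log odds ratio for VPA among patients without ATRA, that is DAC + VPA against DAC. The ATRA coefficient is then DAC + ATRA against DAC. The other two arms contribute nothing to either test.

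An analyst who fits the model as described and reads the Wald test from default output would therefore test something other than the pooled contrast, on half the patients. The reported odds ratios would change meaning in the same way. The Background adds to the ambiguity, because it asks whether a combination "is able to increase the objective best response rate to DAC alone in AML of the elderly", which can be read as a comparison with the DAC arm only.

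At stake is the decision the trial exists to make: whether VPA or ATRA deserves a phase III trial.

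**Working it through.** **Inputs** (Sample size section): response 25% and 40%; one-sided alpha 10% (z = 1.2816); power 80% (z = 0.8416); odds ratio 2; 176 patients calculated (44 per arm); 200 to be randomized (50 per arm).

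**1. The plan's own figure.** Pooled comparison of two rates, chi-square formula without continuity correction:

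n per group = [1.2816·√(2·0.325·0.675) + 0.8416·√(0.25·0.75 + 0.40·0.60)]² / 0.15² = 87.0, rounded up to 88, so 176 in total.

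This reproduces the stated number. Power at 88 against 88 is 80.3%. The odds ratio also checks: (0.40/0.60)/(0.25/0.75) = 2.0.

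**2. The parameter tested when the interaction is in the model.** Write logit(p) = b0 + bV·V + bA·A + bVA·V·A.

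- 0/1 coding: bV = logit p(DAC + VPA) − logit p(DAC).
- ±1/2 coding: bV = the average of that difference and logit p(DAC + VPA + ATRA) − logit p(DAC + ATRA).

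**3. Power with 0/1 coding.** The large-sample variance of one arm's logit is 1/(m·p·(1−p)).

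- m = 44: SE = √[1/(44·0.1875) + 1/(44·0.24)] = √(0.1212 + 0.0947) = 0.465. Then 0.6931/0.465 − 1.2816 = 0.21, so power is 58.3%.
- m = 50: SE = √(0.1067 + 0.0833) = 0.436. Then 0.6931/0.436 − 1.2816 = 0.31, so power is 62.1%.
- Patients needed for 80%: m = (1.2816 + 0.8416)²·(1/0.1875 + 1/0.24)/0.6931² = 4.508·9.5/0.4805 = 89.1, so about 90 per arm and 360 in total.

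**4. Power with centred coding.** SE = ½·√(sum of the four arm variances).

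- Both factors with odds ratio 2 and no interaction: the triple arm has odds (1/3)·2·2 = 4/3, a rate of 57.1%. At m = 44, SE = ½·√(0.1212 + 0.0947 + 0.0947 + 0.0928) = 0.318. Then 0.6931/0.318 − 1.2816 = 0.90, so power is 81.6%.
- Only VPA active (25/40/25/40%): SE = ½·√(2·0.2159) = 0.329, so power is 79.6%.

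**5. Side by side.**

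| Test of VPA | 176 patients | 200 patients |
|---|---|---|
| Pooled 25% vs 40%, chi-square formula | 80.3% | 84.0% |
| Main-effects logistic model, both odds ratios 2 | 81.8% | 85.3% |
| Interaction in model, centred, both odds ratios 2 | 81.6% | 85.2% |
| Interaction in model, centred, only VPA active | 79.6% | 83.3% |
| Interaction in model, 0/1 coding | 58.3% | 62.1% |

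Simulation with 200,000 runs agrees: 60.3–60.5% (176) and about 62% (200) for 0/1 coding; 80.7–82.3% (176) and 84.3–86.1% (200) for centred coding. In the scenarios shown, keeping the interaction term costs almost no power in itself. The loss comes from the parameter that 0/1 coding puts under test.

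**The case against.** The strongest reply is that the estimand is not in doubt. The article states the pooled comparison in two sections, and the Statistical analysis section again speaks of VPA against no VPA and ATRA against no ATRA. Nowhere does the analysis text call DAC + VPA against DAC the tested effect, so an analyst who tested it would depart from the plan. The interaction sentence promises only an estimate and an interval. Coding is also a detail that a full protocol or statistical analysis plan, neither of which is shown, could settle.

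Much of this stands. A reader might infer that the primary tests actually run at about 58% power. The article does not support that, because it specifies no 0/1 coding. A reader might also infer that 176 patients are too few for any logistic model with an interaction. That is wrong: tested on the averaged contrast, the same model keeps about 80–82%. Nor is there a parallel problem in the Cox models, since the article puts no interaction in them.

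What does not stand is that this is merely omitted detail. The article places the interaction in the very model whose treatment terms are tested, and it asserts that the chi-square sample size also serves logistic regression. The two statements agree only under a contrast that it does not name, and common software defaults give the other one.

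**Conclusion.** The concern holds in a conditional form. The pooled contrasts are clearly defined and correctly sized, but the model described for testing them does not identify them. Under 0/1 coding, power falls from the planned 80% to about 58% at the calculated 176 patients, or about 62% with all 200 randomized, and the hypothesis becomes one doublet against DAC alone. Under centred coding or an averaged contrast there is no material loss.

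The figures rest on the article's rates of 25% and 40%, equal arms, and the large-sample Wald approximation, with simulation within about two percentage points at 44 per arm. The 80–82% for the averaged contrast also rests on the article's assumption of no antagonism, taken here as no interaction on the odds ratio scale. The 0/1 result does not depend on that assumption, because it uses only two arms.

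**What to change.** Before the final analysis, choose one of two wordings.

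- **Two models (simplest).** Take both one-sided 10% Wald tests, and the odds ratios reported with them, from a logistic model with main effects of VPA and ATRA. Estimate the interaction and its 95% confidence interval in a separate secondary model.
- **One model.** Keep the interaction in the model, and state that the tested and reported parameters are the effects of VPA and ATRA averaged over the two levels of the other factor, through ±1/2 coding or an explicit contrast.

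In either case, state that the 80% power applies to the averaged contrast. If the unseen analysis plan already does this, it is enough to confirm it.

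The cost is a few sentences. No change to the sample size, the data collected or the Cox models is needed.
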